## Abstract

Background and Purpose: Previous studies have shown that women with GDM can benefit from following dietary recommendations, which are based on food exchange serving (FES) and glycemic load (GL), but compliance with dietary recommendations in women with GDM is not ideal. Therefore, the aim of this paper is to design a dietary intervention program based on behavior change wheel (BCW) to affect GDM women’s compliance with FES based on GL, and to compare the effects of this dietary intervention program versus general dietary management on compliance with dietary recommendations, improving maternal glucose metabolism, and reducing adverse pregnancy outcomes in women with GDM. Methods: This paper is a methodological description of a two-arm randomized controlled trial. In this study, eligible women with GDM will be recruited and divided into the control group (*n* = 30) and the intervention group (*n* = 30). Women with GDM will respectively receive general dietary management (control group) and dietary intervention designed with BCW (intervention group) until after delivery. Information about pregnant women will be collected through questionnaires or prenatal and delivery records. Conclusion: This randomized controlled trial is designed specifically for women with GDM to achieve effective blood glucose control by strengthening GDM women’s compliance with dietary recommendations. If this dietary intervention designed with BCW proves to be effective, then BCW may deserve to be applied to more areas of self-management in women with GDM.

## 1. Introduction

Gestational diabetes mellitus (GDM) has become a new global public health problem. According to the latest data from the International Diabetes Federation (IDF), nearly 17 million pregnant women worldwide currently suffer from GDM [1]. With obesity, advanced gestational age, and sedentary lifestyles becoming more common, the number of women with GDM will continue to increase [2,3]. It is well known that GDM has both long-term and short-term adverse effects on the health of pregnant women and their offspring. These adverse effects include pre-eclampsia, cesarean delivery, and later development of type 2 diabetes in women with GDM [4,5], as well as macrosomia, perinatal mortality, and higher living risk of obesity and type 2 diabetes in offspring born to mothers with GDM [4,6]. To avoid the consequences of GDM, achieving and maintaining euglycemia become the key to care for women with GDM [7].

According to the recommendations of the American Diabetes Association (ADA), the first choice for women with GDM to achieve glycemic targets is lifestyle and behavioral management, which includes medical nutrition therapy (MNT), physical activity, and weight management [8]. Among them, MNT is the most basic link in diabetes treatment [9]. The appropriate nutritional therapy for GDM should aim to ensure the intake of high-quality ingredients to meet healthy pregnancies while achieving euglycemia [10]. However, striking the right balance between the two objectives is a challenge due to the traditional Chinese belief that pregnant women should eat more [11].

The traditional food exchange serving (FES) is a classic meal planning of MNT [12], which is designed according to dietary recommendations. By following the traditional FES, women with GDM can control daily caloric intake and the proportion of three thermogenic nutrients to just enough to meet the needs for healthy pregnancy [12]. Currently, the traditional FES has been widely used in dietary intervention for diabetic patients in East Asian countries [13,14,15], and its effectiveness has been proven [13,16]. However, despite such advantages of the traditional FES, it cannot distinguish differences in glycemic response caused by various foods within the same food type [13]. This leads to the possibility that people with diabetes may still choose foods that have a relatively large impact on blood glucose, although following the traditional FES. Therefore, FES based on glycemic load (GL) was put forward as a new meal planning of MNT [17].

GL was proposed by Salmeron et al. in 1997, which is used to reflect the increasing potential of insulin demand caused by carbohydrates in foods [18]. In 2006, according to dietary habits of Chinese people, Sun et al. developed the new food exchange system based on GL [17]. Different from the traditional FES, FES based on GL suggests that people with diabetes should refer to GL value of each food before selecting foods in the last step of the traditional FES [17]. Existing evidence shows that following FES based on GL could help women with GDM to achieve better results in controlling blood glucose compared to following the traditional FES [19,20]. A meta-analysis of 29 studies also showed that ethnic Chinese women with GDM can benefit from choosing foods with low GL value to improve glucose metabolism and reduce the risks of adverse pregnancy outcomes [21].

The benefits of following dietary recommendations for women with GDM are evident, but whether they actually benefit from it depends on their compliance with dietary recommendations. Mustafa et al. found that only 31.2% of 313 women with GDM in New Zealand had high compliance with dietary commendations by analyzing the matching degree between maternal dietary intake and dietary recommendations [22]. A cohort study conducted in Denmark revealed that only 35% of 336 women with GDM who received MNT were highly compliant with dietary guidelines [23]. In addition, Guo Meiying et al. found that only 46.7% of 139 Chinese women with GDM used the traditional FES to prepare food and control energy intake [24]. Due to these unsatisfactory conditions, it is necessary to design a dietary intervention program that can optimize existing dietary management so as to improve GDM women’s compliance with dietary recommendations.

The Behavior Change Wheel (BCW) is a framework for developing intervention, which is formed by the integration of 19 theoretical frameworks related to behavioral change [25]. BCW has three layers (see Figure 1). Its core is the Capability-Opportunity-Motivation-Behavior system (COM-B system). Michie et al. proposed that capability, opportunity, and motivation are essential conditions to promote the occurrence or change of behaviors [25]. Furthermore, nine intervention functions and seven policy categories are wrapped by layer on the outside of the core [25]. Based on BCW, intervention designers can identify defects in one or more of the three essential conditions in the COM-B system, then effectively select the most appropriate intervention functions that can correct the defects and available policies. Currently, BCW has been used in several health fields, such as community health promotion, health management, and nursing [26,27]. However, BCW has not been used to improve compliance with dietary recommendations among women with GDM.

### Propose

The purposes of this study are to design an intervention program based on BCW to affect GDM women’s compliance with FES based on GL and to compare the effects of this dietary intervention program versus general dietary management on compliance with dietary recommendations, improving maternal glucose metabolism and reducing adverse pregnancy outcomes in women with GDM. This paper is a methodological description of the intervention design and trial protocol.

## 2. Research Hypothesis

We hypothesize that after the intervention, women with GDM who receive the intervention program designed based on BCW will have (1) higher scores of self-management behavior and self-efficacy, (2) better results of maternal glucose metabolism, and (3) lower incidences of common adverse pregnancy outcomes than women with GDM who receive general dietary management.

## 3. Methods

### 3.1. Trial Design and Ethical Approvals

This is a two-arm randomized controlled trial study with parallel designs. The duration of the intervention is expected to take about 6 months. The trial study has been approved by Medical Ethics Committee at Wuhan University School of Medicine (No. 2021YF0048). It was registered by ClinicalTrials.gov on 18 April 2022. The registration number is ChiCTR2200058872.

### 3.2. Research Setting and Participant Eligibility Criteria

The study will be conducted in the obstetric clinic of a Grade 3A hospital in Wuhan, Hubei Province. Pregnant women diagnosed with GDM by a clinical 75 g oral glucose tolerance test (OGTT) at 24 weeks of gestation are eligible to participate. The glucose concentration thresholds of pregnant women accord with IADPSG criteria in 2010 [28]: Fasting blood glucose (FBG) ≥ 5.1 mmol/L and/or 1-h plasma glucose after taking sugar ≥ 10.0 mmol/L and/or 2-h plasma glucose after taking sugar ≥ 8.5 mmol/L. Furthermore, women with GDM who are eligible must meet the following inclusion criteria: (1) Aged between 18 and 40 years, (2) natural pregnancy, (3) singleton pregnancy verified by ultrasound, (4) have adequate cognitive and behavioral abilities, (5) no previous endocrine-related diseases, such as hyperthyroidism, hypothyroidism, and Cushing’s syndrome, (6) voluntarily participate in this study and sign the informed consent form.

### 3.3. Participant Exclusion Criteria

Pregnant women who meet the following criteria will be excluded from the study: (1) Those who have pre-pregnancy diabetes mellitus, (2) ultrasound results showed that the fetus had serious congenital abnormalities, (3) pre-existing pregnancy comorbidities, such as mental illness, heart failure, renal failure, and severe liver disease, (4) existing pregnancy complications, such as severe anemia, threatened abortion and fetal intrauterine growth restriction, (5) using drugs that may affect OGTT results, such as steroids or immunosuppressants, (6) those with a history of smoking, alcohol abuse, or drug abuse, (7) those who have special dietary requirements, such as vegans or those who have special food allergies.

### 3.4. Participant Shedding Criteria

In the following cases, participants will be withdrawn if: (1) Pregnant women who opt to terminate their pregnancy during the study period, (2) pregnant women who do not wish to continue to participate in the study, (3) pregnant women who have difficulties in continuing to participate in this study due to the following physical conditions that happen during the intervention process, such as vaginal bleeding, threatened premature delivery, placental abnormalities.

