## 4. Measures

Primary outcomes for compliance with dietary recommendations include self-management behaviors and self-efficacy of dietary control, and the average daily GL value. Secondary outcomes for maternal glucose metabolism include results of OGTT, FBG, 2 h PBG, and HbA1c. Secondary outcomes for adverse pregnancy outcomes include non-normal gestational weight gain (GWG) (excessive GWG or insufficient GWG), insulin use during pregnancy, cesarean section, premature delivery, macrosomia, and fetal intrauterine growth restriction. The timeliness of data collection is shown in Table 2.

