### 4.5. Pregnancy Outcomes

Information about adverse pregnancy outcomes will be collected from prenatal and delivery records, including excessive GWG or insufficient GWG, insulin use during pregnancy, cesarean section, premature delivery, macrosomia, and fetal growth restriction.

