**Compliance with Dietary recommendations**						
Self-management behavior				√		
Self-efficacy				√		
Average daily GL value			√	√		

Abbreviations: 75 g OGTT, 75 g oral glucose tolerance test; FBG, fasting blood glucose ; 2 h BG, 2 h postprandial blood glucose; GL, glycemic load.

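### Withdrawal for difficulty continuing because of complications such as threatened premature delivery can remove women from the outcome comparison, and the questionnaire primaries are taken only at 37 weeks

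*Protocol article*

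**What the plan says.** Section 3.4 lists three grounds on which participants are withdrawn: the woman ends the pregnancy, she no longer wishes to take part, or, as criterion (3), she has difficulty continuing in the study because of "physical conditions that happen during the intervention process, such as vaginal bleeding, threatened premature delivery, placental abnormalities". All three grounds stand under one rule. Nothing separates stopping the dietary sessions from ending data collection.

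Section 4 gives the secondary adverse pregnancy outcomes as abnormal gestational weight gain and "insulin use during pregnancy, cesarean section, premature delivery, macrosomia, and fetal intrauterine growth restriction". The third part of the hypothesis in Section 2 expects these to be less frequent in the intervention arm. On their source, Section 4.5 says: "Information about adverse pregnancy outcomes will be collected from prenatal and delivery records".

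Section 4 also states: "Primary outcomes for compliance with dietary recommendations include self-management behaviors and self-efficacy of dietary control, and the average daily GL value". In Table 2, self-management behavior and self-efficacy have one tick each, at 37 weeks. Average daily GL has two, at 28 and 37 weeks. FBG, 2 h PBG and HbA1c have an early and a final measurement. Section 4.4 and Table 2 differ on when the early one is taken, but both put the final one at 37 weeks.

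Section 6 names repeated measures MANOVA for what it calls the explored assessment. Section 3.5 sets 30 women per group as a pilot whose results will size a later trial.

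**The concern.** The conditions in criterion (3) arise after randomisation, and one of them leads directly to a listed outcome. If withdrawal means what it appears to mean, women can leave the delivery-outcome comparison because the outcome is approaching. What remains is a subset chosen by an event related to the result, and randomisation no longer protects the comparison.

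The 37-week timing adds a separate loss. A woman who leaves or delivers before that visit has neither questionnaire score, and there is no earlier score to stand in for it. Missingness in two of the three primaries therefore follows a study outcome. The estimates feed into the size of the next trial, so any distortion is carried forward.

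**Working it through.** **No stated figure to reproduce.** The 30 per group comes without an effect size, event rate, power or dropout allowance. The check is a reading of the sections together, followed by illustrations of scale on assumed rates.

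**Step 1: delivery outcomes.** Section 3.4 withdraws on a precursor of premature delivery. Section 4.5 takes that outcome from records that need no active participation. The two fit together only if records are still read after withdrawal, and the article is silent on this. If they are read for every randomised woman, the bias is zero.

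**Step 2: size if records are not read.** Let p be the true preterm rate, w the share of preterm women withdrawn beforehand, and u the share of other women withdrawn (assumed 5% in both arms). The observed rate is p(1−w) / [p(1−w) + (1−p)(1−u)].

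- True rates 10% control and 5% intervention (30 × 0.10 = 3.0 and 30 × 0.05 = 1.5 expected events), w = 50% in both arms: 0.050/(0.050 + 0.855) = 5.5% and 0.025/(0.025 + 0.9025) = 2.7%. The difference falls from 5.0 to 2.8 points.
- Same rates, w = 80% in both arms: 0.020/0.875 = 2.3% and 0.010/0.9125 = 1.1%. The difference is 1.2 points.
- Same rates, w = 80% control and 40% intervention: 2.3% and 0.030/0.9325 = 3.2%. The difference reverses to −0.9 points.
- Equal true rates of 10%, w = 80% in one arm and 40% in the other: 0.020/0.875 = 2.3% and 0.060/0.915 = 6.6%. This is a false difference of 4.3 points, in whichever direction the withdrawals fall.
- The same with equal true rates of 5%: 0.010/0.9125 = 1.1% and 0.030/0.9325 = 3.2%, a false 2.1 points. With 15%: 0.030/0.8375 = 3.6% and 0.090/0.8975 = 10.0%, a false 6.4 points.

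**Step 3: questionnaire primaries.** These are lost whatever is done with the records.

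- Precision: the difference detectable with 80% power at two-sided 0.05 (sidedness assumed) is d = (1.960 + 0.842) × √(2/n). This gives 0.72 for n = 30, 0.76 for n = 27 and 0.81 for n = 24 per arm.
- Bias: suppose 30% of each arm are high-risk women who score δ SD lower, there is no true effect, and all losses come from that group. With a fraction l of the arm lost, the arm mean is −δ(0.30 − l)/(1 − l). For δ = 1, losses of 20% in control and 10% in intervention give −0.222 − (−0.125) = −0.10 SD; for δ = 0.5, −0.05 SD. With losses of 30% and 10% the bias is −0.22 and −0.11 SD. With equal losses it is zero.

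**Step 4: outcomes with two occasions.** For GL, FBG, 2 h PBG and HbA1c, a standard repeated measures MANOVA uses complete cases. A woman with an early value but no 37-week value is dropped altogether.

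**The case against.** Several stronger readings are tempting, and the article does not support them.

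- *Every woman with one of these conditions is withdrawn.* No. The rule covers only those who have difficulty continuing because of the condition. What counts as difficulty is undefined and the list of conditions is open, so the rule leaves room for judgement, but the condition alone does not trigger it.
- *Event rates are understated in both arms.* This cannot be asserted. Records could be read after withdrawal, and the full protocol or analysis plan, neither of which is shown, may say so. What stands is that the published rule, on its natural reading, ends participation and does not close the gap.
- *The intervention arm has more scheduled contact, so withdrawals will differ.* Sections 3.8.1 and 3.8.2 schedule the same number of contacts in both arms: a primary consultation, one online at three days, weekly online sessions and two additional consultations. Only the content differs. Differential withdrawal remains possible because participants and interveners are unblinded (Section 3.7) and the article does not say who decides on withdrawal. It is not shown to be likely.
- *MANOVA drops women from the questionnaire comparison.* The questionnaires have one occasion and no baseline in Table 2, so complete-case loss across occasions, mixed models and ANCOVA on baseline are not relevant to them.

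It can also fairly be said that any 37-week endpoint misses women who deliver earlier, that the adverse outcomes are secondary, and that about three preterm births per arm (on an assumed 10%) support no firm conclusion either way. These points lower the severity. They do not remove the reason to settle what happens to withdrawn women's data.

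**Conclusion.** The point holds as a should-fix. Section 3.4 ties leaving the study to a precursor of a study outcome and does not say that outcome collection continues. For premature delivery and cesarean section this is an ambiguity with a possible bias, which is zero if delivery records are read for all randomised women. For the two questionnaire primaries the loss is certain for any woman withdrawn or delivered before the 37-week visit, because no other value is scheduled.

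The sizes are illustrative only. A false or lost difference of a few percentage points in preterm rate, and up to about 0.2 SD on a questionnaire score under markedly unequal losses, both rest on assumed rates that the article does not give. Confidence is high on the 37-week timing and moderate on the delivery outcomes.

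**What to change.** - In Section 3.4, state that criterion (3) ends the dietary-intervention contacts only and that follow-up continues.
- Take pregnancy outcomes from prenatal and delivery records for all 60 randomised women unless consent to record use is withdrawn, and analyse them in the arm assigned.
- For women who leave the intervention before 37 weeks, obtain the two questionnaires when they stop, where feasible. A last visit before a preterm birth cannot be scheduled in advance, so some values will still be missing. Report the number without a 37-week value by arm.
- For GL, FBG, 2 h PBG and HbA1c, replace complete-case repeated measures MANOVA with a likelihood-based mixed model that keeps women with incomplete data.

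The records are already the data source, so the cost is mainly protocol wording, slightly more data handling, and some questionnaire values taken at an earlier gestational age. The change is needed early, because questionnaire values not collected before delivery cannot be recovered. When the intervention should be stopped for a given woman is a clinical decision and is not addressed here.

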### 3.5. Sample Size

Due to the lack of prior data about applying BCW in dietary intervention in women with GDM, a pilot study will be carried out to provide a comprehensive estimate of the effect size of the intervention. The recruitment goal of the pilot study is 30 pregnant women with GDM for each group [29]. No a priori hypotheses of effect size to identify the ineffectiveness of a comprehensive study were proposed since we considered that the available data were insufficient to create these meaningfully. The minimum sample size for the future study will be calculated based on the results of the pilot study.

### 3.6. Recruitment

Participants will be recruited when pregnant women return to the obstetrics clinic for their 75 g OGTT results. Obstetricians will explain the purpose and significance of this study and emphasize that the trial will be conducted in strict confidentiality. Women with GDM who volunteer to participate in this study will be enrolled immediately after signing the informed consent forms.

### 3.7. Randomization and Blinding

Researchers will use the study website (www.random.org/lists/, (accessed on 19 May 2022)) to create random numbers that correlate to the serial numbers before recruiting participants. The ratio of random allocation is 1:1. Eligible participants will be sequentially recruited and assigned the predetermined random number. Participants with a random number of 1–30 will be divided into the dietary intervention group based on BCW (intervention group), while those with a random number of 31–60 will be divided into the general dietary management group (control group). In this study, participants and interveners will inevitably know the content of the intervention. Therefore, researchers will only ensure the separation of interveners and result assessors.

### 3.8. Randomized controlled trial (RCT) Design

At enrollment, all participants will receive paper guidance materials for dietary control, including a guidebook and the food exchange table. The guidebook records the methods for calculating pre-pregnancy BMI and daily energy requirements for women with GDM (see Supplementary Files S1 and S2), as well as how to convert daily energy requirements into the number of food exchange servings (see Supplementary File S2). The food exchange table shows the GL value and the raw weight of an exchange serving of a certain food. Pregnant women could follow the distribution principles of three major nutrients (daily intake of carbohydrates, protein, and fat account for 50%, 60%, 15%, 20%, and 25–30% of the total energy, respectively. The daily intake of carbohydrate should not be less than 150 g) and the principle of “small and frequent meals” (breakfast, lunch, and dinner + extra 2–4 meals) indicated in the guidebook, and combined with guidance materials to design daily recipes.

#### 3.8.1. Control Group

Pregnant women in the control group will receive general dietary management, including an individual primary consultation at enrollment, two additional consultations at reviews, and online consultations [30,31]. Online consultations will be conducted at three days after enrollment and at 7:00 p.m. every Thursday.

In individual primary consultation, researchers will explain the importance of dietary control, the principles of dietary control, and how to design daily recipes according to FES based on GL to pregnant women in the control group. Researchers will also explain the content of the paper guidance materials to help pregnant women understand the distribution principles of three major nutrients and how to follow the principle of “small and frequent meals”.

In the online consultation at three days after enrollment, researchers will evaluate the dietary behaviors of pregnant women in the past three days and correct the wrong dietary behaviors. In the online consultation at 7:00 p.m. every Thursday, researchers will provide an online guidance team composed of an obstetrician, a dietitian, and two postgraduate nursing students to answer pregnant women’s questions and conduct health education in the WeChat communication group.

In the first addition consultation at the first week after enrollment, researchers will decide on the next phase of dietary management for pregnant women according to the results of fasting blood glucose (FBG) and 2 h postprandial blood glucose (2 h PBG). For pregnant women who need to use insulin, after the clinician has specified the insulin dosage, researchers will adjust pregnant women’s dietary management options in conjunction with the clinician’s advice. For pregnant women who need to make changes to their dietary control, researchers will review pregnant women’s eating behaviors over the past week and correct wrong eating behaviors. For pregnant women who need to stick to the original plan, researchers will not give other guidance.

In the second additional consultation at 28 weeks of gestation, researchers will instruct pregnant women to increase 450 kcal on their daily basal energy requirements calculated from their pre-pregnancy BMI and body energy coefficient [32], so as to properly adjust exchange servings of a certain food.

